### Perceptions of the credibility of the placebo

At the data collection session at the conclusion of course of intervention, the participant will be asked to indicate which intervention (active or placebo) they thought they had received during the last 4 weeks and to give a confidence rating on a scale of 0–10 (with 0=‘not at all confident’ and 10 = ‘extremely confident’ [55]). Global perceived effect will also be measured using a self-assessment of improvement on a seven point rating scale (1 = completely recovered, 2 = much improved, 3 = slightly improved, 4 = not changed, 5 = slightly worsened, 6 = much worsened, 7 = worse than ever) in response to the question ‘How would you rate the course of your ankle complaints since the start of this study?’ [56, 57].

### Other measures

Telephone interviews will be conducted monthly after enrolment up to 1 year to record any new injuries, any treatments undertaken, and the level of engagement in sports and other activities. These variables will be used as covariates in the analysis of the 12 month follow-up data as they are possible confounders. Further, the Beighton score for hypermobility and radiographic measurement of the anterior drawer stress test will be recorded.

#### Beighton score

Scoring for joint hypermobility will be undertaken according to previously published methods [36]. Each participant will be assessed in five test positions, as follows:Passive extension of the fifth metacarpophalangeal (MCP) joint to ≥90 degrees. The participant sits on a chair at the short side of the table with the shoulder in 80 degrees abduction, elbow flexed at 90 degrees, and the forearm resting on the table in a pronated position. The fifth MCP joint is passively extended by the researcher and a goniometer is used to measure the angle.Passive hyperextension of the elbow ≥10 degrees. The participant sits on a chair with the shoulder at 90 degrees of flexion and the forearm supinated. A goniometer is placed at the lateral epicondyle and the measurement is taken at maximum elbow extension.Passive hyperextension of the knee ≥10 degrees. The participant lies supine with their legs in the horizontal plane. The goniometer is placed at the lateral femoral condyle and the measurement taken at maximum knee extension.Passive apposition of the thumb to the flexor side of the forearm. The score is positive if the entire thumb touches the flexor side of the forearm while the shoulder is flexed at 90 degrees, the elbow extended, and the forearm pronated.Forward flexion of the trunk with the knees straight. The score is positive if the participant’s hand palms rest easily on the floor.

#### Anterior drawer stress test with radiographic measurement

Ankle joint mechanical instability will be assessed using a lateral x-ray to measure the amount of anterior translation of the talus during a ligament stress test for each ankle. The radiograph will be taken while the ankle is undergoing a simulated anterior drawer test using 125 N force [38]. The stress radiograph will be taken with the participant in a supine lying position with the foot relaxed in a resting position and the lower leg resting on a support, with the hip and knee each flexed approximately 45 degrees. The heel will be supported on a dynamometer (Lafayette Manual Muscle Tester, Model 01165, Lafayette, IN, USA) attached to a customised device which produces the anteriorly directed force. The distal tibia will be fixed on the support using a stabilising belt placed over the distal aspect of the tibia [58]. The central ray will be centred just above the tip of the lateral malleolus and perpendicular to the image receptor [59]. Then an anterior force of 125 N will be applied [38] to the heel of the participant at an angle of 20 degrees to the vertical plane as per recommended clinical practice [60], using the customised device. The force will be monitored using the digital display of the dynamometer attached to the customised device, and the radiograph will be taken at 125 N. The ankle radiograph will be taken at the focal-film distance of 110 cm [61] and will set to 55 kVp and 2.1 mAs. The same procedure will be applied to the other ankle. These images will be taken at the baseline data collection session to assess mechanical instability for use in subgroup analysis.

Radiographic images will be digitally obtained using Merge PACS™ software (Merge Health Care, 2012). Anterior translation of the talus will be measured between the posterior lip of the tibial articular surface and the nearest point of the talar dome (Fig. 3) [61–64] to identify any mechanical instability. Anterior drawer stress radiographs have been found to have moderate sensitivity, high specificity and a high positive predictive value for the evaluation of lateral ankle instability [37]. A between-limb difference of 3 mm in anterior translation of the talus or an absolute value of 10 mm is considered clinically significant [37].

**Fig. 3 Fig3:**
[figure not shown]
Anterior translation of the talus during the anterior drawer stress test is measured as the distance on X-ray from the posterior lip of the tibial joint surface to the nearest point of the talar dome (left ankle, 13.2 mm in this image)

### Application of the intervention

Participants in the experimental group will be treated with a manual MWM technique to the ankle and will be taped after the intervention using the Mulligan approach [22] to attempt to maintain the effects of the MWM. The control group will receive a detuned (inactive) therapeutic laser treatment to the lateral region of the ankle. The number of treatment sessions delivered for each participant will be based on their symptomatic response to treatment, as determined by the clinical judgement of the treating practitioner. Each participant will be asked to avoid concurrent interventions during their participation in the study.

### MWM intervention

The participant’s inferior tibio-fibular joint will be mobilised using Mulligan’s fibula MWM for dorsiflexion and/or inversion [22]. Initially, the technique will be performed in supine lying with the tibia resting on the treatment table and the foot unsupported off the table’s edge. The practitioner applies a sustained pain-free anteroposterior glide with a slight cephalad and lateral inclination to the distal fibula (lateral malleolus). This glide is maintained while the participant performs active inversion or dorsiflexion (depending on which is more limited in range) to end of range. There should be no pain with the active movement. At the end of range, the practitioner will apply and sustain overpressure to the active movement for a few seconds (or the participant will do so after appropriate instruction) [16, 22]. If dorsiflexion remains restricted, this technique can be progressed and performed in partial and/or full weight-bearing.

One treatment session will consist of three to five sets, with six to ten repetitions of the active movement in each set, with the actual dosage depending on the individual response of the participant [22]. Participants will receive between two to eight sessions according to the clinical reasoning of the practitioner, over a period of 4 weeks. After each session, Mulligan MWM taping will be applied in an attempt to replicate the sustained fibula glide [8]. Non-elastic tape will be applied to the ankle starting 2 cm anterior to the fibula and 1 cm proximal to the tip of the lateral malleolus. The tape will be spiralled obliquely around the lower limb while the fibula glide is sustained, finishing on the anterior aspect of the leg [22]. The participant will be instructed to keep the tape on for 24 h. In the case of an adverse reaction, they will be advised to remove the tape immediately and note the length of time the tape was in place.

### Detuned laser intervention

The placebo intervention will be applied using a detuned therapeutic laser device (Meyer Medical Electronics, Mordialloc, Australia) for 5 min to the lateral region of the ankle, maintaining the probe 0.5–1 cm away from the skin [31, 65–67]. The detuned laser device will appear to function normally (both audibly and visually) to participants, but no effective emission will be produced. Both the participant and the practitioner will be required to wear protective glasses as per normal clinical practice [66, 68]. Participants will receive two to eight treatments over 4 weeks, according to the clinical judgement of the treating practitioner. Detuned laser has been used in several other studies assessing manual therapy including for chronic ankle sprains. It avoids any possible direct mechanical effects to the ankle being treated and also does not activate somatosensory receptors [69–71]. Further, it has been shown to have a strong placebo effect [70]. Scheduling of participant appointments will be arranged to avoid interaction between participants.

## Sample size and data analysis

Previously published data related to the primary outcome measure of function (FAAM subscales, ADL and sports) [18, 34] (MCID = 8.0, SD = 5.68; MCID = 9.0, SD = 7.42 respectively) were used in sample size calculations [18, 34, 72]. A sample size of 16 per group allowing for a 30% drop-out rate was estimated, for a minimal statistical power of 0.80 and an alpha significance level of 0.05. Secondary analysis based on the subgroups of ankle instability (mechanical, functional) will be preliminary in nature as the study is not powered for this aim.

Data will be analysed using SPSS Statistics for Windows (Version 23.0, Armonk, NY, IBM Corp). Continuous data will be assessed for normality using the Shapiro-Wilk test.

Baseline comparability between groups will be analysed using the independent t-test or non-parametric equivalent, as appropriate. Linear mixed models will be used to analyse the outcome measures. For the primary outcome measure, ‘function’ will be the outcome variable and time, group and an interaction term for time by group will be the predictors. Any statistically significant difference in change in the outcome variable over time between the groups will be indicated by the *p* value for the interaction term. Pairwise Bonferroni comparisons will be performed to explore the differences between time points and between groups if a significant interaction is identified. Independent t-tests will be used to compare outcome measures between groups at each time point and the changes of the scores will be used to detect any changes in the outcomes of interest. Intention to treat analysis will be performed with all participants allocated to each group condition to evaluate the effect of the independent variable. For missing data in ITT analysis, a participant’s last observation for each outcome measure will be carried forward. The average number and the average duration of intervention sessions between groups will be compared. If any significant difference observed, secondary analysis will be taken to find any correlation between the treatment volume and the outcomes.

Additional variables recorded during monthly phone interviews (new injuries, changes in activity level, and occurrence of other treatments) will be used as covariates in the analysis of the 12 month follow-up data as they are possible confounders. Further, the Beighton score for hypermobility will also be included in regression analysis as a covariate.

Radiographic measurement of the anterior drawer stress test will be used to differentiate subgroups of CAI in potential sub group analysis.

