Consenting participants will be randomised into two groups: an experimental group who will receive MWM, and a control group who will receive a placebo (detuned laser). All of the participants will be assessed for general joint hypermobility using the Beighton score [36]. Mechanical ankle instability will be tested separately for each ankle using an X-ray while undergoing an anterior drawer stress test [37, 38]. The clinically important outcome measures will include; radiological imaging of fibular position with respect to the tibia (positional fault), dorsiflexion range of motion (DFROM), pressure pain threshold (PPT), pain intensity, function, static balance and dynamic balance. These procedures and outcome measures are further explained below. The researcher who collects the clinical measurements, and the radiographer taking the X-rays, will be blinded to the participant’s group (intervention) allocation. This researcher will remain blinded to the group allocation until the 3 month follow-up. The 12 month follow-up data will be collected using online questionnaires.

Each participant will be randomly allocated to a group to receive either MWM (active) treatment or detuned laser treatment (placebo) (these interventions are fully explained below). The participant will be blinded as to whether they are receiving an active or placebo intervention, however due to the nature of the interventions, the treating practitioner cannot be blinded. Participants will be randomly allocated to groups according to a computer generated (GraphPad Software, Inc., CA, USA) randomisation schedule by another researcher not involved in data collection using sealed opaque envelopes. Each envelope will contain a piece of paper printed with either ‘1’ or ‘0’, for which ‘1’ denotes ‘MWM’ group and ‘0’ denotes ‘placebo’ group. The treating practitioner will open the envelope and allocate the participant to a group according to the number in the envelope, and deliver the designated treatment accordingly.

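### With 30% drop-out, 16 per group gives about 77% power on FAAM Sport by the t-test, slightly below the stated minimum of 0.80

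*Protocol article*

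**What the plan says.** The section on sample size and data analysis in the protocol article takes its inputs from "Previously published data related to the primary outcome measure of function (FAAM subscales, ADL and sports"), namely "MCID = 8.0, SD = 5.68; MCID = 9.0, SD = 7.42 respectively". The result reads: "A sample size of 16 per group allowing for a 30% drop-out rate was estimated, for a minimal statistical power of 0.80". Alpha is set at 0.05. The section gives no formula and no sidedness, and it does not divide alpha between the subscales.

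For the analysis, the same section tests the primary outcome through the time-by-group interaction in a linear mixed model. It adds: "Independent t-tests will be used to compare outcome measures between groups at each time point". Drop-outs stay in the intention-to-treat analysis with their last value carried forward.

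**The concern.** A stated minimum power should hold for the more demanding of the two subscales on which the trial was sized. That is Sport, with the smaller standardised difference. The drop-out allowance implies 11 completers per group, and at that size the choice between a normal approximation and a t-test decides whether power is above or below 0.80.

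At stake is how a null Sport result would be read. The discussion section says the trial was powered for the effect on the functional outcome, so readers will set a null result against the stated 0.80.

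**Working it through.** **Inputs** (all from the sample size paragraph unless marked)
- ADL: 8.0/5.68, so d = 1.408
- Sport: 9.0/7.42, so d = 1.213
- 16 per group, 30% drop-out, power 0.80, alpha 0.05
- Assumed: two-sided test, equal loss in both arms, and the quoted SDs apply to the quantity compared between groups

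**1. Reproducing the plan's figure.** Normal approximation: n per group = 2 × (1.960 + 0.842)² / d².
- ADL: 7.91, so 8; 8/0.7 = 11.4, so 12
- Sport: 10.67, so 11; 11/0.7 = 15.7, so 16

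The stated 16 is therefore the Sport requirement by the large-sample formula with the correct drop-out inflation. By that formula, power for Sport at 11 per group is Φ(1.213 × √(11/2) − 1.960) = Φ(0.885) = 81.2%.

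**2. Completers.** 16 × 0.7 = 11.2, so 11 per group.

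**3. Power by the t-test.** Noncentral t with 2n − 2 degrees of freedom and noncentrality d × √(n/2). At n = 11 there are 20 degrees of freedom, the critical value is 2.086, and the noncentrality is 3.303 (ADL) and 2.845 (Sport).

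| Completers per group | ADL | Sport |
|---|---|---|
| 11 | 88.1% | 77.2% |
| 11 and 12 | not needed | 79.1% |
| 12 | 90.9% | 81.0% |

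If loss is random at 30% in each arm, so that the number of completers varies, average power for Sport is 76.9%.

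**4. Requirement for Sport.** Twelve completers per group are the fewest that reach 80%. From 16 that is retention of 12/16 = 75%, or a loss of at most 25%. At 30% loss it would take 12/0.7 = 17.1, so 18 per group.

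**5. Size of the gap.** 81.2% − 77.2% = 4.0 points from the approximation; 80% − 77.2% = 2.8 points below the stated minimum.

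**6. Two subscales together.** By simulation at 11 per group, for an assumed between-subscale correlation of 0.5 to 0.8:
- both significant at 0.05: about 72% to 75%
- at least one significant at 0.025: about 88% down to 84%

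**The case against.** **The number is not a slip.** Sixteen follows exactly from the plan's inputs by a standard formula, and that formula gives 81% at 11 per group. This stands: a reader might infer a mistaken drop-out inflation, but the document shows none. What remains is that the approximation is too optimistic at 20 degrees of freedom, and the plan's own between-group comparisons are t-tests.

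**All 16 are analysed.** With last values carried forward, 16 per group enter the analysis, and nominal t-test power for Sport is 91%. That holds only if carried-forward values show the full treatment effect. The plan itself allowed for drop-out, so it treats those participants as lost information. As an illustration, suppose the 30% leave before the post-treatment assessment, so that their change is zero, and take 7.42 as the SD of change. Power at 16 per group is then about 72% by simulation. Carrying values forward does not secure the claim.

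**The primary test is a mixed model.** Its power depends on within-person correlations that the article does not give. The t-test is the benchmark that the stated inputs allow.

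**Alpha splitting.** A reader might infer that power on Sport is only 66%, which is the value at alpha 0.025 with 11 per group. The document states alpha 0.05 and no split, so this is not a property of the plan. Nor does it follow that every rule for the two subscales misses 0.80: success on either at 0.025 reaches about 84% to 88%.

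**Conclusion.** The point holds, and it is small. Under the plan's own inputs and a two-sided 0.05 t-test, the stated minimum of 0.80 is met for ADL (88%) but not for Sport (77%) once 30% have dropped out. The deficit is about 3 points on one subscale, and it disappears if at least 12 per group are retained.

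The conclusion rests on a two-sided test and on counting completers only. With a one-sided 0.05 test, Sport at 11 per group would have 86%, so stating the sidedness matters. The figures for the two subscales together also rest on the assumed correlation. Nothing here shows that the trial is seriously underpowered or that 32 participants is untenable.

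**What to change.** Keep 32 participants and restate the power. Suggested content: with 16 randomised per group and 30% loss, 11 completers per group give 88% power for FAAM ADL and 77% for FAAM Sport (two-sample t-test, two-sided 0.05); 80% for Sport requires at least 12 completers per group, a loss of at most 25%.

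State the formula and the sidedness. Say which success rule applies to the two subscales and quote the power that belongs to it, with the assumed correlation: about 72% to 75% if both must succeed at 0.05, or about 84% to 88% if either at 0.025 suffices.

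The cost is wording only. Recruitment is unchanged, and the published figure becomes slightly less favourable.

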## Discussion

One proposed anatomical mechanism underpinning MWM is theorised to be a correction of a minor bony incongruity (positional fault) which is at the source of the patient’s presenting problem [22, 73]. The existence of an anterior fibular ‘positional fault’ in individuals with CAI has some preliminary radiological support [27]. There are also limited MRI data supporting Mulligan’s positional fault hypothesis in cases of lateral ankle pain [72], however there is no evidence to date that MWM reverses any positional anomaly. Further, should any fibular positional anomaly be reversed immediately after the application of MWM, the length of time this reversal or correction is maintained is unknown. The proposed study protocol is designed to determine the presence of any positional fault of the fibula in CAI, and whether MWM can reverse this, and if so, whether this reversal is evident 4 weeks after treatment commences. Moreover, this study protocol will explore the correlation between an anatomical measure (fibular position) and other clinical outcomes (pain, function, pressure pain threshold, DFROM, static and dynamic balance). Potential relationships between these measures may help explain how changing an anatomical measure may effect a clinically meaningful outcome. The effect of MWM in CAI will also be explored in relation to the presence or not of radiologically measurable mechanical instability.

There are very few clinical trials with long term follow-ups which have assessed MWM for any musculoskeletal condition, and only one for CAI which had a 6 month follow-up [6, 15]. The proposed study protocol is therefore the first designed to evaluate the long term effectiveness of MWM on CAI. Moreover, the treatment effect may depend on the type of instability present (mechanical or functional), and this study protocol may evaluate the efficacy of MWM on these two subgroups of CAI. However, the subgroup analysis will be exploratory as the study was only powered to detect the main effect being the intervention on the functional outcome.

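### Unadjusted t-tests at each time point sit beside a gated, Bonferroni-adjusted procedure for the same comparison, and the two FAAM subscales share one 0.05 with no rule for combining them

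*Protocol article*

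**What the plan says.** All the analysis text is in the protocol article, Sample size and data analysis.

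- **Primary outcome.** The sample size rests on the "primary outcome measure of function (FAAM subscales, ADL and sports"), with planning values "MCID = 8.0, SD = 5.68; MCID = 9.0, SD = 7.42 respectively". The error rate appears once, in the sample-size sentence: "for a minimal statistical power of 0.80 and an alpha significance level of 0.05".
- **Test tied to the primary outcome.** Function is modelled on time, group and their interaction. The p value of the interaction is said to show whether the groups differ in change.
- **Gated follow-up.** "Pairwise Bonferroni comparisons will be performed to explore the differences between time points and between groups if a significant interaction is identified".
- **Next sentence, ungated.** "Independent t-tests will be used to compare outcome measures between groups at each time point". The same sentence adds that changes of the scores will be used to detect changes in the outcomes of interest.
- **Visits.** Under Procedure, FAAM is due at baseline, end of intervention, week 12 and, as a self-report measure, month 12.
- **Exploratory label.** Only the analyses by type of instability are called preliminary or exploratory. The Discussion adds that "the study was only powered to detect the main effect being the intervention on the functional outcome".

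**The concern.** Two consecutive sentences ask whether the groups differ at a given visit and answer under opposite rules. One is conditional on the interaction and Bonferroni-adjusted. The other is unconditional and unadjusted. Because the second has no exploratory label, a reader of the results could not tell whether a significant t-test at one visit supports the primary claim when the interaction is not significant.

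The two subscales add to this. With one alpha of 0.05 and no split, order or both-must-succeed rule, even a strict interaction-only reading gives two chances of success.

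What is at stake is whether the 5% error rate applies to the claim about function, and whether the choice of rule could be made after the data are seen.

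**Working it through.** **1. Reproduce the planned size** (two-sided 0.05 assumed, since sidedness is not stated; power 0.80; normal approximation; n = 2(1.96+0.842)²(SD/MCID)² per group).

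- Sport: 2 × 7.85 × (7.42/9.0)² = 10.7, so 11; 11/0.7 = 15.7, so 16.
- ADL: 2 × 7.85 × (5.68/8.0)² = 7.9, so 8; 8/0.7 = 11.4, so 12.

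The Sport figure gives the stated 16 per group. The arithmetic is sound for one two-group comparison on one subscale at 0.05. The problem is error control.

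**2. Count the tests on function that the text states.**

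- Interaction: one per subscale, so 2.
- Score t-tests: 2 subscales × 3 post-baseline visits = 6.
- Change-score t-tests: the clause gives neither test nor visits. Read broadly it adds 6, making 12 t-tests.

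**3. Upper guide if tests were independent:** 1 − 0.95^k.

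- k = 2: 9.8%
- k = 6: 26.5%
- k = 12: 46.0%

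These are too high because the tests are correlated.

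**4. Simulation with no effect.** The article gives no correlations. Assumed: between visits 0.5-0.7 (compound symmetry), between subscales 0.6-0.8; 11 or 16 per group; 20,000 trials per setting. The interaction is tested by a repeated-measures F on 3 df.

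| What may decide | Chance of at least one p<0.05 |
|---|---|
| Interaction, one subscale | 5% |
| Interaction, either subscale | 8-9% |
| Any of six score t-tests | 17-22% |
| Any of twelve t-tests (scores and changes) | 31-37% |

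In about 14-18% of these null trials a score t-test is significant while neither interaction is. Results for 11 and 16 per group agree within about one percentage point. Widening the between-subscale correlation to 0.5-0.9 gives 7-9%, 15-22% and 29-37% for the last three rows.

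**5. Power if the two subscales are controlled together** (noncentral t, 11 completers per group, from 16 × 0.7 = 11.2).

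- Sport: 0.77 at 0.05; 0.66 at 0.025.
- ADL: 0.88 at 0.05; 0.80 at 0.025.

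Under Holm, Sport lies between its two values, because it is tested at 0.05 once ADL has been rejected at 0.025.

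**The case against.** The best defence is that the primary test is named. Only the mixed model is introduced for the primary outcome, and the interaction p value is given as the indicator of a group difference in change. The t-test sentence speaks of outcome measures in general and does not say it decides anything. On that reading the three follow-ups sit inside one omnibus test and add no inflation. The excess comes from the two subscales alone, at 8-9%. This stands as the most natural reading, but the text does not exclude the other: the t-tests carry no exploratory label, although the instability subgroup analyses do.

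A second defence is that the order of subscales and the primary time point are commonly left to an analysis plan that is not shown. That is fair for the time point, whose absence is not the point here. It does not cover two conflicting rules that the article itself states.

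Two stronger readings are tempting and are not supported:

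- **Twelve unadjusted t-tests.** The change-score clause does not say that t-tests on change are run at every visit for both subscales. The count clearly in the text is six.
- **An underpowered interaction test.** The sample size was not derived for the 3-df interaction, but no clear shortfall follows. With SD 7.42, 11 per group, compound symmetry and a 9-point Sport effect that lasts, fades or vanishes after the first follow-up, power is 0.78-0.97 at between-visit correlations 0.5-0.7, against 0.77 for the single t-test. It falls to 0.62-0.66 only at an assumed 0.3. The plan also carries last observations forward for all allocated participants, so 11 is not the planned analysis set. At 16 per group power is at least 0.81 in all these settings, before any dilution from carried-forward values.

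**Conclusion.** The concern holds in a limited form. The article names the interaction as the test for the primary outcome and makes it the gate for adjusted pairwise comparisons. It then adds ungated, unadjusted t-tests for the same between-group comparisons without saying that they cannot support the primary claim. It also leaves two primary subscales under a single 0.05.

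The error rate is about 8-9% if only the interactions decide and about 17-22% if any of the six score t-tests may. The 31-37% figure applies only under the broad reading of the change-score clause. The sizes rest on assumed correlations, but two or more tests with an either-may-succeed rule exceeded 5% in every setting tried. If both subscales had to succeed, having two would add no inflation, but no such rule is stated.

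A reader might also infer that the end-of-intervention visit should be the confirmatory one. The documents do not support that: the objective in the Background includes long-term effectiveness, so the choice of visit belongs to the investigators.

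**What to change.** Change the wording of Sample size and data analysis:

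1. Delete the separate independent t-tests and the change-score clause, or label them exploratory and not a basis for the primary claim.
2. Take the visit-specific group differences, with 95% confidence intervals, from the mixed model.
3. State one confirmatory test: either the interaction, or a group contrast at one visit that the investigators choose before seeing data.
4. Control FAAM ADL and FAAM Sport together, for example with Holm, or name one as primary.

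No new data are needed. The cost is in the power statement. With Holm, Sport power for a two-group comparison at 11 completers per group lies between about 0.66 (alpha 0.025) and 0.77 (alpha 0.05), and this should be written down. If 0.80 were required for Sport at 0.025, the normal approximation gives 13 evaluable per group, and 13/0.7 = 18.6, so 19 randomised. The t-based calculation gives 15 evaluable, and 15/0.7 = 21.4, so 22 randomised. Naming one subscale as primary keeps alpha at 0.05 and avoids this loss.
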